**Accelerated substudy**

In a subgroup of patients (n=167), participants will be consecutively approached for co-enrollment to undergo an additional accelerated stress-perfusion protocol on the same scanner, performed in a randomized order within a short time interval (ideally ≤1 week) of the standard CMR (NCT05221762). The accelerated protocol will consist of (1) stress and rest perfusion assessment (dual-sequence T1-weighted saturation-recovery gradient echo sequence), (2) volumetric assessment (free-breathing, multi-slice, retrogated real-time cine sequence), and (3) LGE (non-breath-hold, single-shot inversion-recovery gradient echo sequence) (sequences *described in CMR protocol section)*. In the accelerated scan, rest perfusion will be performed at the end of the study to permit a stress-LGE only assessment. Blinded image analysis will involve an initial qualitative read (cine, LGE, and stress perfusion) by two independent expert readers acting in consensus, followed by visual assessment of the quantitative perfusion data (*described in CMR image analysis section*). The primary objective is to determine whether the accelerated protocol achieves non-inferior diagnostic accuracy compared with standard stress-perfusion CMR in diagnosing significant CAD at the per-vessel level. Other key secondary objectives include comparison of patient-level diagnostic performance and determining whether the accelerated protocol improves time efficiency, cost-effectiveness, and patient tolerability. A sample size of 150 participants is required to achieve 90% power (α significance 5%) to demonstrate non-inferiority of the accelerated protocol to standard CMR at the per-vessel level, with a non-inferiority margin of 5%. To allow for missing data in up to 10%, 167 participants will be recruited.

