**Stress T1 mapping substudy**

In a subgroup of patients (up to n=150) the discriminatory ability of T1 reactivity to detect territories subtended by significant CAD will be explored [53]. Consecutive participants will be co-enrolled to undergo native (rest and stress) and post-contrast T1 mapping at the basal, mid-ventricular, and apical levels of the left ventricle (matched slice locations as perfusion imaging) using a breath-hold, ECG-gated modified Look-Locker inversion-recovery sequence with a 5(3)3 acquisition scheme (typical sequence parameters: TE 1.06 ms, TR 274.8 ms, slice thickness 8 mm, matrix 256 × 144, FOV 360 mm, FOV phase 85.2%, flip angle 35°) [54]. To minimize artifact, shimming will be centered on the left ventricle and tightly planned around each slice prescription. Stress T1 maps will be acquired at peak vasodilator stress prior to perfusion imaging. T1 maps will not be considered as part of the perfusion assessment for the primary or secondary outcomes. The primary objective is to determine the diagnostic accuracy of T1 reactivity (percentage increase in T1 from rest to stress) and stress T1 in detecting significant CAD at the per-vessel level, using invasive FFR (FFR_inv_) as the reference standard. Other key objectives include comparison of patient and segmental level diagnostic performance of T1 metrics using both invasive and non-invasive reference standards and exploring the associations with quantitative perfusion indices. For sample size estimation, assuming a CAD prevalence of 50% and accuracy of 85% for CMR and 80% for stress T1 mapping, 337 complete vessel pairs are required for 80% power (α significance 5%) to demonstrate superiority of stress-perfusion CMR over stress T1 at the per-vessel level, assuming no more than 10% discordant pairs. Furthermore, this sample size also provides 90% power to demonstrate superiority of stress-perfusion CMR at the per-vessel level, assuming an accuracy of 85% for CMR and 75% for stress T1 mapping, with no more than 20% discordant pairs.

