The primary analysis population will comprise all patients with complete ICA and both CMR and CCTA/FFR_CT_ (excluding patients with incomplete data). Overall accuracy of CMR and CCTA/FFR_CT_ for detecting significant CAD at the patient level will be compared using the Newcombe–Wilson score method for calculating a two-sided 95% confidence interval for the difference in accuracy [62]. The primary study and substudies will be reported in accordance with the ‘Standards for Reporting Diagnostic Accuracy Studies’ (STARD) guidelines. Secondary analyses population will utilize all patients with appropriate data for each analysis. Diagnostic performance (sensitivity, specificity, predictive values) for detecting significant CAD at per patient and vessel level will be compared by using exact binomial tests and the weighted generalized score methods [63], [64]. Logistic regression models will be applied to investigate factors associated with diagnostic performance of each method, at the patient level (e.g., age, sex, pre-test probability of CAD) and vessel level (e.g., degree of stenosis, FFR); vessel-level analyses will use mixed effects regression to adjust for patient-level clustering. The overall performance of the methods will be compared, placing different weights on false positive and false negative results. Responses to questionnaires about experiences of the two scans will be summarized and compared using appropriate paired analysis methods. Similar methods will be applied for the analysis of substudies, leveraging the within-patient design to maximize power wherever possible.

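### Vessel-level comparisons are assigned exact binomial tests that ignore clustering within patients, and the stress T1 substudy's 80% power at 337 vessel pairs holds only if vessels are independent

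*Protocol article*

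**What the plan says.** The Protocol article, section 2.15 (Statistical analysis), states that diagnostic performance, meaning sensitivity, specificity and predictive values, "at per patient and vessel level will be compared by using exact binomial tests and the weighted generalized score methods". The next sentence introduces logistic models of factors associated with each method's performance and ends, after a semicolon, with "vessel-level analyses will use mixed effects regression to adjust for patient-level clustering". The paragraph closes with "Similar methods will be applied for the analysis of substudies, leveraging the within-patient design to maximize power wherever possible".

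Both CMR substudies in section 2.6.2 have per-vessel primary objectives. The stress T1 mapping substudy enrols up to 150 patients and states that "337 complete vessel pairs are required for 80% power (α significance 5%) to demonstrate superiority of stress-perfusion CMR over stress T1". It adds that the same number gives 90% power for 85% against 75% accuracy with at most 20% discordant pairs. The accelerated substudy states that "A sample size of 150 participants is required to achieve 90% power (α significance 5%) to demonstrate non-inferiority of the accelerated protocol", per vessel, with a 5% margin, and recruits 167 to allow for 10% missing data. Neither substudy states an intra-patient correlation, a design effect or the number of vessels per patient. The accelerated substudy also gives no discordance rate.

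**The concern.** An exact binomial (McNemar-type) test counts each discordant pair as an independent coin toss. Vessels from one patient share a scan, a hyperemic response, an image quality and a consensus read, so one test may beat the other in several vessels of the same patient at once. If that correlation is positive, the problem appears in one of two ways. Analysed without adjustment, p-values are too small and intervals too narrow. Analysed with adjustment, the effective number of pairs falls and the planned power is not reached.

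The clause on mixed effects shows that the authors know vessels cluster. Read in place, however, it governs the regressions on factors associated with performance, not the tests that compare the modalities. The per-vessel secondary comparisons are at stake, and so are the substudy conclusions, including a non-inferiority claim, if the similar methods are applied there at vessel level.

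**Working it through.** **Inputs from the article.** T1 substudy: "accuracy of 85% for CMR and 80% for stress T1 mapping" (difference 0.05), "assuming no more than 10% discordant pairs" (0.10), alpha 5%, 337 pairs. Alpha is taken as two-sided; sidedness is not stated, but two-sided reproduces the figure. Accelerated substudy: 150 participants, 90% power, margin 0.05.

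**Assumptions not in the article.** Three vessels per patient (m = 3), and an intra-patient correlation rho of the signed between-test difference, shown over a range. Design effect DE = 1 + (m − 1) × rho = 1 + 2 × rho.

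**Step 1. Reproduce 337.** The unconditional power of the two-sided exact binomial test on independent pairs (difference 0.05, discordance 0.10) is 79.93% at 336 pairs and 80.07% at 337. So 337 is the first number that reaches 80%. The asymptotic McNemar formula gives 312, and continuity-corrected versions give 331 to 352. The T1 figure is therefore the exact independent-pairs calculation, with no clustering allowance.

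**Step 2. T1 power with clustering.** Exact power is evaluated at the effective number of pairs, N / DE. The required number of vessels is 337 × DE, rounded up.

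| rho | DE | Power at 337, 85% v 80% | Power at 450, 85% v 80% | Power at 337, 85% v 75% | Vessels needed for 80% (85% v 80%) |
|---|---|---|---|---|---|
| 0 | 1.0 | 80.1% | not computed by the exact test | 98.6% | 337 |
| 0.05 | 1.1 | 75.4% | 88.2% | 97.6% | 371 |
| 0.10 | 1.2 | 71.2% | 84.8% | 96.4% | 405 |
| 0.20 | 1.4 | 63.5% | 77.8% | 93.3% | 472 |
| 0.30 | 1.6 | 56.9% | 71.2% | 89.5% | 540 |

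The 450 column assumes that all 150 patients give three complete vessel pairs. The largest design effect it can absorb is 450 / 337 = 1.335, so rho = (1.335 − 1) / 2 = 0.17.

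**Step 3. Type I error of the unadjusted exact test.** Simulation of 150 patients × 3 vessels with 10% discordance and nominal two-sided 5%:

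| rho | Type I error |
|---|---|
| 0 | 3.6% |
| 0.05 | 4.6% |
| 0.10 | 5.4% |
| 0.20 | 7.8% |
| 0.30 | 9.7% |

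A separate simulation of 20,000 replicates gave 3.4%, 5.6%, 7.6% and 9.8% at rho 0, 0.10, 0.20 and 0.30, which agrees. The exact test is conservative under independence, so its error passes 5% only from a correlation just below 0.1.

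**Step 4. Accelerated substudy.** The recruitment figure reproduces: 150 / (1 − 0.10) = 167. The 150 itself cannot be reproduced, because discordance is not given. Using n = (1.96 + 1.2816)² × discordance / 0.05²:

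- At 10% discordance, n = 10.507 × 0.10 / 0.0025 = 420 independent vessels.
- Solving for 150 × 3 = 450 vessels gives discordance = 450 × 0.0025 / 10.507 = 10.7%.

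So 150 participants fits 450 independent vessels at about 10 to 11% discordance. If that was the basis (10.7%), power is about 87%, 84%, 78% and 73% at rho 0.05, 0.10, 0.20 and 0.30.

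**The case against.** The strongest reply has four parts.

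- **Clustering is acknowledged and the article is condensed.** The clause on mixed effects is worded broadly, weighted generalized score methods are named beside the exact tests, and section 2.16 says analysis starts only after the SAP is final. What stands is that details may be settled there. But the article does name a test for vessel-level comparisons, and that test assumes independence. Whether the score methods handle clustering cannot be checked from the article, and naming them does not make the exact test valid for clustered vessels. At the least, the two sentences need to be reconciled.
- **The quoted sentence covers sensitivity, specificity and predictive values, whereas the substudy primaries concern accuracy.** This is fair: the reference to similar methods does not strictly commit the substudies to an exact binomial test. But the T1 size was computed with that test on independent pairs. The main study's accuracy method, a Newcombe–Wilson interval specified for patients, would raise the same question if applied to vessels.
- **A reader might infer that vessel-level error rates are too high in general and that the stated powers hold only at zero correlation.** The figures do not support that. At a correlation of 0.05 the exact test is still below 5%. The 90% T1 claim starts at 98.6% and is still 89.5% at 0.30. The 150-patient cap could also supply enough vessels for the 80% claim up to a correlation of about 0.17, although the text does not reserve that surplus for clustering.
- **A reader might also infer that both substudies were sized on independent vessels.** This is shown for T1 only. The accelerated figure fits other inputs with clustering included: 8% discordance needs 336 vessels, leaving a design effect of 450 / 336 = 1.34, and a one-sided 5% test at 10% discordance needs 343, leaving 450 / 343 = 1.31.

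**Conclusion.** The point holds in limited form. The article assigns vessel-level comparisons a test that treats vessels of one patient as independent, and the only clustering adjustment it states sits with the regression models. The 337 pairs for 80% power contain no clustering allowance, so at 337 pairs any positive correlation takes that power below 80%.

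The size of the effect rests on two assumptions, three vessels per patient and the value of the correlation, and neither is in the article. For the accelerated substudy the evidence is consistency only. The primary analysis is at patient level and is untouched. The point is therefore below must-fix: a correction to secondary and substudy analyses, to be settled before the SAP is final.

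**What to change.** - For vessel-level comparisons of the modalities, and for the accelerated substudy's non-inferiority interval, name a paired method that accounts for clustering by patient: GEE with patient-robust variance, a clustered McNemar test, or a bootstrap that resamples patients. Keep exact tests at patient level.
- State whether the clause on mixed effects covers only the regressions, so that it no longer appears to answer for the comparisons.
- Restate the T1 80% power and the accelerated power with the assumed correlation, vessels per patient and discordance. For T1, state the number of vessels expected from up to 150 patients. With 450 vessels the 80% claim holds up to a correlation of about 0.17, so the cap need not rise.

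The cost is SAP wording and a restated power calculation. The analysis becomes valid without more patients. The downside is slightly wider vessel-level intervals.

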### Measures to minimize bias

2.16

Selection bias will be minimized through consecutively approaching suitable patients. Clinically indicated ICA will be performed by cardiologists blinded to imaging data. CMR and CCTA reporters will be blinded to all patient characteristics, the results of ICA and other imaging tests. Image anonymization will be performed by an independent administrator, and unblinding codes held by staff independent from investigators. Statistical analysis will be undertaken by an independent Clinical Trials Unit (University of Glasgow) and started after finalization of the statistical analysis plan and database lock.

### Study timetable

2.17

Ethics and regulatory approval was secured in October 2019. Study enrollment commenced in November 2020 and is expected to be completed in September 2025. A further 12 months will be allowed for data analysis, statistical analysis, manuscript preparation, and final report.

## Strengths and limitations

3

The strengths of CONCORD include its prospective design with blinded reporters for each modality, independent from investigators responsible for participant recruitment, study procedures, and data collection. These rigorous blinding procedures will ensure all image analyses are reported without knowledge of patient characteristics and results of other imaging tests, while an independent Clinical Trials Unit will oversee the statistical analyses. Limitations include its conduct in a single-center, expert CMR research facility, confined to higher field strength (3-Tesla, due to availability of specified sequences), which may limit wider generalizability. Furthermore, patients will have been clinically referred for diagnostic ICA prior to participation in the study, and thus are considered at a higher risk for CAD. Therefore, our findings may not be generalizable to lower-risk populations. Finally, although FFR_inv_ serves as the reference standard, it may be underestimated in patients with concomitant CMD, which is not routinely confirmed invasively. The CONCORD study will assess the diagnostic performance of each imaging strategy, necessitating a future comparative evaluation focused on clinical outcomes.

## Summary

4

The CONCORD study is a prospective, single-center head-to-head diagnostic accuracy study that will comprehensively evaluate two frontline non-invasive functional imaging modalities in patients with suspected angina referred for ICA. Currently, there are no prospective, robust, head-to-head comparisons of these two functional imaging modalities. Given the discordance between guidelines on the optimal diagnostic algorithm in patients at a moderate-to-high risk of CAD, confirmation of non-inferior diagnostic performance of CCTA/FFR_CT_ would support its widespread adoption in these patients. However, if non-inferiority is not demonstrated or if quantitative CMR proves superior, this will merit a careful consideration of optimum diagnostic strategy, considering diagnostic performance, cost, patient preference, and geographical provisions of imaging services.

